## Abstract

**Background:**

Ecological momentary assessments (EMA) are ideal for capturing the dynamic nature of young adult substance use behavior in daily life and identifying contextual risk factors that signal higher-risk episodes. These methods could provide a signal to trigger real-time intervention delivery. Study compliance and engagement are common barriers to participation but may be improved by personalizing messages. This study compares compliance outcomes between one group of young adults receiving standard (generic) prompts at each assessment and another group that received additional personalization and an updated data dashboard (DD) showing study progress to date at 1 randomly selected prompt per day.

**Objective:**

The primary objectives are to (1) develop a real-time DD for giving participants personalized updates on their progress in the study and (2) examine its preliminary overall effects on study compliance and experiences. Secondary objectives are to identify person-, day-, and moment-level characteristics associated with study compliance and person-level characteristics associated with perceived usefulness of the DD.

**Methods:**

This is a protocol for Project ENGAGE, a 2-arm randomized controlled trial. Arm 1 (EMA group) is engaged in a standard EMA protocol, and arm 2 (EMA+DD group) is engaged in the same study but with additional personalization and feedback. Inclusion criteria are (1) previous participation in a recent college student survey about health behavior and mental health who indicated willingness to participate in future research studies and (2) indicated past-month alcohol use; lifetime marijuana, hashish, or Delta-8-tetrahydrocannabinol (THC) use; or some combination of these on that survey. All participants in this study completed a baseline survey; EMA at 11 AM, 2 PM, 5 PM, and 8 PM each day for 21 days; and an exit survey. Participants in arm 2 engaged in a microrandomized trial, receiving a personalized DD at 1 randomly selected prompt per day. Primary outcomes include whether a survey was completed, time to complete a survey, and subjective experiences in the study. Primary analyses will compare groups on overall study compliance and, for arm 2, use marginal models to assess the momentary effect of receiving 1 updated DD per day.

**Results:**

Approval was granted by the university’s institutional review board on February 8, 2023. Recruitment via direct email occurred on March 30 and April 6, 2023; data collection was completed by April 29, 2023. A total of 91 individuals participated in the study. Results have been accepted for publication in *JMIR Formative Research.*

**Conclusions:**

Results from the evaluation of this study will indicate whether providing (at randomly selected prompts) real-time, personalized feedback on a participant’s progress in an EMA study improves study compliance. Overall, this study will inform whether a simple, automated DD presenting study compliance and incentives earned to date may improve young adults’ compliance and engagement in intensive longitudinal studies.

**International Registered Report Identifier (IRRID):**

DERR1-10.2196/57664

## Introduction

### Overview

The prevalence of alcohol and cannabis use peaks in young adulthood (age range approximately 18-25 years), with 31% of young adults reporting recent heavy episodic drinking (5+ drinks in a row) and 11% reporting daily or near-daily cannabis use [1]. Heavy and frequent use in this age group can be linked with risk for alcohol use disorders, cannabis use disorders, or combined alcohol and cannabis use disorders, with 16.4% of young adults meeting criteria for a past-year alcohol use disorder and 16.5% meeting criteria for a past-year cannabis use disorder [2]. Far more common are the numerous acute substance-related harms that young adults experience from heavier alcohol use, cannabis use, or combined alcohol and cannabis use episodes in daily life, such as social-interpersonal issues, physical effects, and memory impairments [3].

Real-time data capture, as in daily diary studies or ecological momentary assessment (EMA) studies, is ideal and widely used for identifying antecedents and consequences of days and moments of highest alcohol- and cannabis-related risk [4]. Such intensive longitudinal data methods can be used to distinguish between- and within-person effects by asking questions such as “Are individuals who experience more stress more likely to report binge drinking?” (between-person) and “Are individuals more likely to report binge drinking on days when they experience more than their usual stress?” (within-person). Such methods are also ideal for capturing the dynamic nature of substance use behavior in daily life and identifying contextual risk factors that signal higher-risk episodes. Using such methods could ultimately provide a signal to trigger real-time intervention delivery.

However, compliance—particularly in substance use studies—can be a major concern for several reasons. First, young adults are less likely to complete reports on weekends when substance use is more likely to occur [5,6] and thus most critical to assess. Second, particular types of substance use behaviors, such as combining alcohol and cannabis, occurs somewhat rarely [7]. These behaviors can only be captured with many days of assessment, but participant compliance and motivation to participate in the study protocol may wane over time. Third, to assess behavior in optimal windows and provide timely intervention content, in some cases it is critical to assess behavior *in the moment when risk factors are higher*. However, engagement in the study protocol has the potential to interfere with participants’ daily lives. If young adults feel burdened by intensive longitudinal data collection, they may be less likely to provide complete data. A meta-analysis by Jones et al [8] concludes that overall, EMA compliance is only approximately 75% among individuals who use substances. Few studies have examined ways to improve participant compliance during intensive longitudinal data collection, yet recent work suggests that personalizing messages to young adults may increase compliance [9].

Mobile health apps have been developed in efforts to improve symptoms related to mental health, substance use, and a variety of other chronic health conditions and health behaviors. Many of these apps have shown no efficacy and/or modest clinical effects [10]. Poor engagement and related factors (eg, compliance, retention, and dropout) likely contribute to these findings because poor engagement with intervention content greatly weakens therapeutic effects. Only recently have studies of mobile health apps included measures of engagement as important outcomes; some even include aspects of engagement as the focus of interventions [11,12]. Among a wide variety of mobile health apps for managing chronic conditions (eg, mental well-being and HIV medication adherence), a meta-analysis estimated that the pooled dropout rate across apps was 43%, though the duration (range: 2 weeks to 1 year) and characteristics of study design varied considerably [13]. In another meta-analysis of apps addressing mental health problems, the dropout rate was approximately 36% after 8 weeks [11].

One way to improve young adult compliance may be to provide personalized, updated progress reports throughout their study participation, such as a data dashboard (DD) with real-time feedback on their progress in a study or aspects of the participant’s current or recent characteristics or behaviors. Personalization may be particularly useful because it can provide timely information unique to the person. Personalization may be operationalized in a variety of ways and may include content that serves self-interest or prosocial goals. For example, Carpenter et al [14] implemented a trial in which participants received biweekly messages about accrued reward points for a chance to win a prize for themselves (self-interest messages) or a chance to win a prize to donate to a charity (prosocial messages) and compared compliance rates. Interestingly, self-interest messages were more effective for compliance early in the study, and prosocial messages were more effective later in the study [14]. Thus, providing personalized data-driven feedback, particularly with the goal of improving compliance, is an understudied but particularly useful area of investigation.

To better understand study engagement and begin to address limitations in prior research, we enrolled young adults in a 2-arm randomized controlled trial called Project ENGAGE. Both groups participated in a 21-day EMA study that included 4 survey prompts per day (up to 84 prompts total). Participants were randomized to either participate in a traditional EMA study, where standard text prompts with links to a survey were received 4 times per day (EMA group), or an augmented study condition in which the text prompt was accompanied by a DD for 1 randomly selected survey per day throughout the EMA protocol (EMA+DD group). This 2-group design allows us to examine the overall effect of receiving 1 DD per day on overall study compliance and engagement. Individuals assigned to the EMA+DD group participated in a microrandomized trial (MRT) [15], which allows us to examine the short-term effects of the DD on momentary study compliance and inform the development of a just-in-time intervention that could be deployed to maximize study compliance within individuals.

### Aims and Objectives

#### Primary Objectives

The primary objectives of Project ENGAGE are to (1) develop a platform or delivery system for providing real-time, personalized updates on progress in the study and (2) examine the preliminary overall effects of embedding this real-time DD on study compliance and experiences. Intervention group differences will be examined in terms of the overall number of completed surveys (out of 84 prompts), average time to submit completed surveys, and subjective experiences with the study protocol. For the second aim, primary outcomes include participants’ overall compliance with the 84 surveys, mean time to complete a survey after receiving a prompt, and user experiences with the DD system.

#### Secondary Objectives

Secondary outcomes are to identify person-, day-, and moment-level characteristics associated with study compliance and person-level characteristics associated with perceived usefulness of the DD:

The following person-level characteristics will be examined in relation to study compliance overall and as moderated by the treatment group: baseline characteristics (gender, first and second vs third and fourth year in college, and history of substance use) and weekly app use.We will estimate differences in compliance outcomes (did or did not complete all 4 surveys that day and mean time to complete surveys that day) as a function of day in study (days 1-21) and whether it was a weekday or weekend.We will compare differences in momentary compliance and time to respond to a prompt across the following moment-level characteristics: whether the participant reported using their phone at the time they received the prompt, and (for the EMA+DD group) time of day on which the DD was received.

This study will yield didactic information for the broader research community on how to deploy a real-time DD or messaging system in a smartphone-based EMA study to improve ongoing participant compliance. Additionally, this study will demonstrate how to collect and analyze data from a study that uses an MRT embedded within a 2-arm randomized controlled trial.

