Each prompt was sent at 4 equally spaced times per day (11 AM, 2 PM, 5 PM, and 8 PM) for 21 days, for a total of 84 prompts for each participant. Assessment timing was fixed to ensure data collection protocol as identical between both groups, to allow time in between assessments or avoid stacking of assessments, and to accommodate typical sleeping schedules and timing of substance use among our sample of college students who use substances*.* At each prompt, participants reported their substance use since the last prompt, psychosocial factors, and whether they were using their phone at the exact moment of receiving each prompt. Participants were instructed to complete each survey within 60 minutes of receiving the link, at which point the link would expire. At the conclusion of the 21-day portion of the study, participants completed an exit survey to provide feedback on their experiences in the study, including the acceptability and usefulness of a DD (for the EMA+DD group) or their openness to receiving a DD (for the EMA group).

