Participants were given 1 hour to complete each survey after receiving the invitation via text. The invitation links in the text messages took the participant to the server and forwarded them to the relevant REDCap survey only if the link was clicked within the designated timeframe and the participant had not already completed that prompt.

At 11 AM on the day following the 21st day of the EMA study, all participants in both groups received a link to an exit survey, which assessed their experiences while participating in the study. Participants had 7 days to complete the exit survey.

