### Outcome Measures

#### Primary Outcomes

This study focused on 2 objective measures of compliance and a set of quantitative and qualitative measures of subjective experiences. Primary outcomes included the following:

Overall compliance: overall compliance was derived from a moment-level binary measure of compliance (ie, an indicator of whether the participant completed the survey within 60 minutes of a particular prompt), summed across 84 prompts within an individual. This was used to address the question: “Did individuals who received a daily DD complete a greater number of surveys, on average, compared to those who did not?”Average time of survey response: average time was derived from the length of time between the survey prompt and survey completion (among completed surveys), averaged across up to 84 prompts. This outcome was used to address the question: “Did participants who received the DD complete surveys more quickly, on average, compared to those who did not?”Subjective experiences of the study protocol: subjective experiences were assessed in the exit survey and were compared across groups. This comparison relied on both quantitative and qualitative measures of experiences.

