#### Secondary Outcomes

Total number of surveys completed within each week, to compare whether participants were more likely to comply to the EMA protocol during week 1, 2, or 3, and whether the intervention effect varied across weeks.Mean time to complete surveys (among completed surveys) within each week.Total number of surveys completed within each day, to compare whether participants were more likely to comply to the EMA protocol across days 1 through 21, and whether they were more likely to comply on weekdays versus weekends. These differences also were examined to see whether the intervention effect varied across days or types of days.Mean time to complete surveys (among completed surveys) within each day.The moment-level binary indicator of compliance and moment-level length of time to complete each survey will be used as outcomes in multilevel models examining moment-level predictors of compliance (eg, time of day and whether they completed last survey) and moment-level predictors of time to complete surveys (eg, whether currently using phone, stress, positive affect, and negative affect). Group assignment will be included as a moderator to see whether the intervention effect varies across types of moments.(For the EMA+DD group only) Themoment-levelbinary indicator of compliance and moment-level length of time to complete each survey will be examined in relation to whether the DD was included at that prompt.

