## Results

Recruitment invitations were sent via direct email to 411 individuals. Of these, 92 (22%) completed the consent form, completed the baseline survey, and were randomized to either the EMA group or the EMA+DD group. Among these individuals, 91 (99%) ultimately participated in the EMA survey (ie, provided data at 1 or more EMA prompt), thus determining our final sample size. Data were collected during March and April 2023.

Participants were predominantly White (92%), non-Hispanic (89%), and female (67%), with a mean age of 20.3 (SD 1.18) years. Among the 91 participants, 43 (47%) were randomized to the EMA group and 48 (53%) were randomized to the EMA+DD group. Overall study compliance was very good, with a mean of 64.3 (14.6) out of 84 (76.5%) prompts completed, resulting in a total of 5896 (out of a possible 7644) person-moments of data.

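### Momentary compliance cannot be compared by self-reported phone use, because phone use is an item of the survey whose completion defines compliance

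*Protocol article*

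**What the plan says.** All references are to the protocol article.

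- **Secondary Objectives** names two outcomes for the moment-level analysis: "We will compare differences in momentary compliance and time to respond to a prompt across the following moment-level characteristics". The first characteristic listed is "whether the participant reported using their phone at the time they received the prompt". As written, both outcomes are to be compared by phone use.
- **Participants and Trial Design** says how phone use is obtained. At each prompt participants report, alongside substance use and psychosocial factors, "whether they were using their phone at the exact moment of receiving each prompt". No passive or device-based measure is described.
- **Primary Outcomes** defines moment-level compliance as "an indicator of whether the participant completed the survey within 60 minutes of a particular prompt".
- **Study Implementation** says the link forwards to the survey "only if the link was clicked within the designated timeframe and the participant had not already completed that prompt", so an unanswered prompt cannot be filled in afterwards.
- **Secondary Outcomes** pairs outcomes and predictors differently. For compliance it gives "moment-level predictors of compliance (eg, time of day and whether they completed last survey". For response time it gives "moment-level predictors of time to complete surveys (eg, whether currently using phone, stress, positive affect, and negative affect". Phone use appears only in the second list.

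**The concern.** The predictor is a self-report inside the survey, and the outcome is whether that survey was completed. A participant who does not answer leaves no record of phone use, so the predictor is observed essentially only when the outcome equals 1. This is neither a power problem nor a modelling detail that a fuller analysis plan could supply. The contrast between compliance while using and while not using the phone is not identified from the data described.

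An explicitly stated secondary comparison would then produce either no estimate or one fixed by how missing values are handled. The same section also says the study will show other researchers how to collect and analyse data from this kind of design, which is a further reason to get the sentence right.

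**Working it through.** **Inputs.** From Results: 91 participants, a mean of 64.3 of 84 prompts completed (76.5%), and "a total of 5896 (out of a possible 7644) person-moments of data". The share of prompts at which the phone was in use is not reported. Where it is needed below, it is an assumption shown over a range.

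**1. Reproduce the stated totals.**
- Possible prompts: 91 × 84 = 7644, which agrees exactly.
- Completed prompts from the mean: 64.3 × 91 = 5851, against 5896 stated. The difference is 45 (0.8%). As percentages, 5896/7644 = 77.1% and 64.3/84 = 76.5%.

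**2. Count the prompts without a phone-use value.**
- From the total: 7644 − 5896 = 1748, and 1748/7644 = 22.9%.
- From the mean: 7644 − 5851 = 1793, and 1793/7644 = 23.5%.

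So about 1750 to 1790 prompts were missed, and essentially all of them lack the item.

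**3. Cross-classify.** Among prompts with phone use recorded in a completed survey, compliance is 5896/5896 = 100%. It is 100% for those using the phone and 100% for those not using it, so the difference is zero by construction.

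**4. Allow for partial or late surveys.** The 60-minute check is applied when the link is clicked, whereas compliance requires completion within 60 minutes. A survey opened in time but left unfinished, or finished late, could hold the item with compliance equal to 0. No count is given. Assume k such records:
- k = 45: 5896/(5896 + 45) = 99.2% compliance among prompts with the item; 45/1748 = 2.6% of missed prompts.
- k = 200: 5896/(5896 + 200) = 96.7%; 200/1748 = 11.4% of missed prompts.

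The outcome is still almost constant, and the few zeros come only from people who had opened the survey. They say nothing about phone use at prompts that were ignored.

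**5. What the data leave open.** Let s be the share using the phone among completed prompts and u the share among missed prompts; u is unobserved. Then
- compliance, using = 5896s / (5896s + 1748u)
- compliance, not using = 5896(1 − s) / (5896(1 − s) + 1748(1 − u))

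The difference (using minus not using) falls steadily as u rises, so u = 0 and u = 1 give its limits:

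| s (assumed) | difference at u = 0 | difference at u = 1 |
|---|---|---|
| 0.3 | +29.8 points | −49.7 points |
| 0.5 | +37.2 points | −37.2 points |
| 0.7 | +49.7 points | −29.8 points |

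For s = 0.5 and u = 0: 2948/2948 − 2948/(2948 + 1748) = 1 − 0.628 = 0.372. The data described cannot settle even the sign.

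**The case against.** The strongest reply is that Secondary Outcomes already makes the right split. Its examples for compliance are known whether or not the prompt is answered, and its examples for response time come from answered surveys. On that reading, the Secondary Objectives sentence is merely condensed. Part of this stands: the mismatch may be one of wording, and the workable version is already in the document. But both lists are given as examples, so they do not withdraw a comparison stated outright elsewhere. For the same reason this is a mismatch and not a strict contradiction.

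A second reply is that little depends on it. That is right as to scale. The failure is confined to the compliance half of one secondary comparison in what the authors call a feasibility study. Response time by phone use can be estimated among completed surveys, and the time of day of the dashboard is known at every prompt.

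A reader might infer three stronger things that the documents do not support:
- *That the plan will report a large false association.* This would follow if missing phone use were coded as not using, but no such coding is proposed. A complete-case fit would show a constant outcome, which an analyst would notice at once.
- *That the flaw undermines decisions on when to send a just-in-time prompt.* The Introduction and Discussion tie just-in-time development to the microrandomized trial, whose exposure is dashboard delivery, not phone use.
- *That every missed prompt lacks the item without exception.* Partial or late surveys are possible, and the two completion figures differ by about 45, so the accurate wording is essentially all.

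**Conclusion.** The comparison of momentary compliance by same-prompt phone use is wrong as written. The predictor is missing at essentially all of the roughly 1750 to 1790 missed prompts, about 23% of 7644. Compliance among prompts with the item is about 100% in both groups, or 97% to 99% if 45 to 200 partial or late records are assumed.

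The conclusion rests on one reading: that phone use is known only through the momentary survey. That is the only source the article describes. It does not depend on the phone-use shares assumed above, which only illustrate how much is left undetermined.

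Severity is moderate. The primary outcomes, the comparison between randomized groups and the microrandomized dashboard contrast are unaffected.

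**What to change.** In Secondary Objectives, restrict phone use to time to respond among completed surveys, and bring the sentence into line with Secondary Outcomes. For momentary compliance, use only predictors known at every prompt whether or not it is answered: time of day, day in study, weekday or weekend, and completion of the previous prompt.

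If phone use carried forward from an earlier completed survey is used as a predictor of compliance, label it as a different question. That value may be hours or days old and does not describe the participant when the current prompt arrived.

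The cost is one sentence in the objectives and the matching line in the analysis. No new data are needed. Data collection is finished, so the change governs only analysis and reporting.
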